#### Methods in analysis to handle protocol non-adherence and any statistical methods to handle missing data

2.8.2

Study adherence is defined as participation in all sessions according to group assignment and completion of at least 80% of the tasks in the booklet. Non-adherence is noted if participants fail to complete more than 20% of the tasks. Therapists use a standardized checklist to document which components were completed or omitted and note the reasons for any deviations (e.g., if the content of the session was too demanding). Adherence is monitored by attendance at sessions, documentation by therapists, and self-reports by patients. Recruitment continues for each group and clinic until the required 14 patients have met the adherence criterion.

The primary outcome, the WAI, must not contain any missing values. All other questionnaires are evaluated in accordance with their manuals, and individual missing values are treated or imputed as described in the manuals.

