#### Explanation for the choice of comparators

2.5.1

Throughout the study, all three study groups participate in regular psychosomatic rehabilitation and receive treatment as usual (TAU) in accordance with the guidelines of the German pension insurance for patients with PCS. The control group (group 1) receives only TAU, while the other two groups additionally receive one of the two interventions (group 2 = JOURNAL group; group 3 = FRAME group). Although participants are assigned to groups according to a sequential cohort design, systematic differences or changes in symptom burden should be minimal and attributed to group affiliation and whether a study intervention was received. Which group participants are in depends solely on the timing of their rehabilitation, not on other systematic differences. (see **Figure 1**). Patients are informed about the study on the first day in the rehabilitation hospital. All treating providers are aware of the participants’ condition assignments.

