##### Group 2 – Intervention group “JOURNAL”

2.5.2.1

Patients in group 2 receive TAU and an extra intervention consisting of two short appointments (sessions) lasting no more than 20 minutes. The main point of this intervention is that patients should write down their expectations and imaginations as independently as possible and without assistance from others, e.g. a therapist. Patients in the JOURNAL group are given an accompanying booklet as part of the study, which summarizes the most important information from the individual sessions. The booklet also contains illustrations and worksheets and is the same as in the FRAME group. The booklet is distributed to patients in group 2 on the first days of the rehabilitation by a research assistant who was trained by the team in Ulm. Patients are asked to reflect on their individual expectations of therapy in writing. The individual sessions in which the booklet is discussed include specific reflection questions and exercises designed to help patients process their personal expectations and challenges. In detail, the booklet contains two tasks in which patients are asked to reflect on their expectations, an imagination exercise, and a list of enjoyable activities for after rehabilitation. When leaving the rehabilitation clinic, patients are allowed to take the journal home with them. Only a documentation form completed by the research assistant remains at the clinic.

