#### Criteria for discontinuing or modifying allocated interventions

2.5.3

In the event of an acute or significant deterioration of symptoms, including the onset of suicidal tendencies, the intervention will be either modified or discontinued. The decision on this matter rests with the treating therapist or physician at the rehabilitation clinic, who will discuss this with the patient. In such cases, the rehabilitation clinic will initiate appropriate therapeutic treatment. Participants also retain the right to withdraw from the intervention at any time and for any reason, without providing justification. Withdrawal from the study – for whatever reason - has no impact on the rehabilitation measures for patients.

Selection bias cannot be ruled out in studies, especially in real-life studies. The interventions are designed in such a way that we expect a low dropout rate and plan to recruit the calculated sample size. Due to data protection regulations, the data of patients who have dropped out cannot be used for *post-hoc* analysis.

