#### Sample size

2.5.9

A total sample of N = 84 participants will participate in one of three groups: a control group receiving treatment as usual only (TAU), a JOURNAL group, and a FRAME group, with 28 individuals in each group. Case numbers are based on the following facts: In general, hardly any studies have been published on the effectiveness of psychosomatic rehabilitation measures for patients with PCS (42). Initial studies show medium to large effects, depending on the outcome variable. For example, effects were observed for somatoform complaints (d=0.60) and the 6-min walking test (d=1.22) (6). No study could be found that showed effect sizes for changes in earning capacity or ability to work. Rief et al. (26) found a large effect size (approximately d=1.0, calculated from the data in the article) for improvements in limitations and the subjective assessment of ability to work in hours (approximately d=2.0, calculated from the data in the article) through the intervention to optimize expectations in patients undergoing bypass surgery. As the patients in this study are already undergoing psychosomatic rehabilitation treatment, the intervention is an add-on that may not show a statistically large effect (Cohen’s d > 0.8). Therefore, the sample size should be large enough to detect a medium effect. Furthermore, it should be possible to test the effectiveness of each intervention compared to the treatment as usual (TAU) group. For a 2x2 analysis of variance with repeated measures (ANOVA; 2 groups x 2 time points) for the change in the main outcome measure (e.g., WAI) from admission to discharge, with a mean effect size of f=0.25 and a power of 0.95, N = 54 patients are required for the comparison of TAU with one of the intervention groups (calculated with G*Power 3.1.9.6; freeware from Kiel University). In order to compare the second intervention group with the TAU group, further N = 54/2 = 27 patients are required in this group. In total, this equates to N = 81 patients. To be able to divide these patients between the two clinics and the three groups, a total of N = 84 patients are required, for whom at least admission and discharge data are available. This means that the sample is also sufficiently large for 2x3 ANOVAs (2 groups x 3 time points; N = 36 required). In summary, we plan to conduct two 2×2 ANOVAs, specifically using a mixed-design ANOVA (two-factor ANOVA with one repeated-measures factor and one between-group factor). With an estimated drop-out rate of 20%, 100 patients must be recruited.

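### Section 2.8.2 fills every cell with 14 adherent patients, but only JOURNAL and FRAME patients can fail the adherence criterion, and Section 2.5.9 defines the same 84 without it

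*Protocol article*

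**What the plan says.** All references are to the protocol article.

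- **Criterion (2.8.2).** To count as adherent, a patient needs "participation in all sessions according to group assignment and completion of at least 80% of the tasks in the booklet." A second sentence looks at tasks only: "Non-adherence is noted if participants fail to complete more than 20% of the tasks." The two differ for a patient who misses a session but completes 80% of the tasks.
- **Stopping rule (2.8.2).** "Recruitment continues for each group and clinic until the required 14 patients have met the adherence criterion."
- **Who can be assessed on it (2.5.1).** "The control group (group 1) receives only TAU, while the other two groups additionally receive one of the two interventions." Study sessions and the booklet are described only for JOURNAL (2.5.2.1) and FRAME (2.5.2.2).
- **Reasons for non-completion.** Sections 2.5.4 and 2.8.2 name content that is too demanding; 2.5.4 adds concentration difficulties. Under 2.5.3, after an acute or significant deterioration, "the intervention will be either modified or discontinued."
- **Required sample (2.5.9).** "a total of N = 84 patients are required, for whom at least admission and discharge data are available." Adherence is not mentioned there. Section 2.9.1 gives 42 participants per site.
- **Analysis (2.8.1, 2.8.2).** Each intervention group is compared with TAU in a 2x2 ANOVA of WAI from admission to discharge. The WAI may have no missing values. No sentence says what happens to non-adherers whose WAI is complete.

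**The concern.** Adherence is observed after baseline and plausibly depends on fatigue, cognition and early course, which also drive change in the WAI. A cell filled by counting adherers, when only two of the three arms can produce a non-adherer, selects on a post-baseline variable on one side of each primary comparison. Section 2.5.1 defends the non-randomised design on the ground that group membership depends only on when rehabilitation took place. An analysed sample filtered by adherence in two arms would no longer have that property.

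The rule also affects calendar time. Groups are recruited one after another in each clinic (2.6). An intervention cohort that has to replace non-adherers stays open longer than the TAU cohort, which widens the calendar differences that a sequential design already carries.

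**Working it through.** **1. The plan's own sample size.** Inputs from 2.5.9: f = 0.25, power 0.95, two groups, m = 2 time points. Alpha = 0.05 and a correlation of rho = 0.5 between time points are assumed, because the article states neither. For the time-by-group interaction,

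lambda = f² x N x m / (1 - rho) = 0.0625 x 54 x 2 / 0.5 = 13.5, with df = 1 and 52.

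Power is 0.942 at N = 52, 0.950 at N = 54 and 0.957 at N = 56, so 54 reproduces. Then 54 + 27 = 81, rounded up to 84.

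**2. The quota is the required sample.** 3 groups x 2 clinics x 14 = 84, or 28 per group. Per site, 3 x 14 = 42, as in 2.9.1. Adherence therefore decides who fills the planned sample.

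**3. Bias if non-adherers are left out.** With two time points the interaction test is the two-sample t test on change scores. Suppose there is no true effect, the least adherent fraction q is replaced in the intervention arm only, and adherence propensity correlates r with WAI change. With z_q the q-quantile of the standard normal distribution and phi its density,

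spurious difference (SD of change) = r x phi(z_q) / (1 - q).

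For q = 0.20: phi(z_q) / 0.80 = 0.350, so r = 0.3 gives 0.105 and r = 0.5 gives 0.175. Two-sided rejection rates at 28 per group:

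| q | r | Spurious benefit (SD) | Type I error |
|---|---|---|---|
| 0.10 | 0.2 | 0.04 | 5.2% |
| 0.10 | 0.3 | 0.06 | 5.5% |
| 0.10 | 0.5 | 0.10 | 6.5% |
| 0.20 | 0.2 | 0.07 | 5.8% |
| 0.20 | 0.3 | 0.10 | 6.8% |
| 0.20 | 0.5 | 0.17 | 10.1% |
| 0.30 | 0.2 | 0.10 | 6.6% |
| 0.30 | 0.3 | 0.15 | 8.6% |
| 0.30 | 0.5 | 0.25 | 15.6% |

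A simulation of 20,000 trials per row agreed (for example 5.3% in the first row and 15.8% in the last). Both q and r are assumptions; the article supports no value for either.

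For scale, f = 0.25 under the assumptions of step 1 corresponds to 1.0 SD of change (lambda = 0.25N = d²N/4, so d = 1.0). The bias is therefore 4% to 25% of the effect the trial is sized to detect.

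**4. Recruitment under the quota.** Each intervention cell needs 14 / (1 - q) patients, rounded up, and each arm has two cells: 32 per arm at q = 0.10, 36 at 0.20 and 40 at 0.30, against 28 in TAU, all before ordinary drop-out. At q = 0.20 the total is 36 + 36 + 28 = 100. That is already the whole recruitment target in 2.5.9, which was set for drop-out.

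**The case against.** The strongest reply is that 2.8.2 states when enrolment of a cell ends, not who is analysed. Read literally, a cell may run past 14 and non-adherers with T1 and T2 WAI may stay in the ANOVA. Analysis sets are also commonly left to the statistical analysis plan, which is not shown. This stands in part. A reader might infer that non-adherers are certainly excluded, but no sentence says so. What remains is a quota equal to the required sample, which makes sense only if adherers are the patients who count, and which is not the definition in 2.5.9.

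Four other readings go further than the text allows:

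- **Deteriorating patients are always replaced in the intervention arms and kept in TAU.** An intervention may be modified rather than discontinued, and a modified course may still meet the criterion. TAU also loses patients who withdraw (2.7.2) or lack a complete WAI.
- **One omitted booklet item makes a patient non-adherent.** Section 2.5.2.1 lists the booklet's contents, but the scoring units behind the 80% are not given and the manual is to be published separately.
- **Section 2.5.9 counts patients regardless of adherence.** It is silent on adherence, and its data requirement is worded as a minimum. The two sections need aligning; they are not in outright contradiction.
- **The 20% drop-out figure is the non-adherence rate.** It is overall drop-out across the sample, so it cannot serve as a source for q.

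The authors also acknowledge possible selection bias (2.5.3) and call the results preliminary (3.1). That tempers the interpretation but does not remove a one-sided rule that is easy to avoid.

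**Conclusion.** The concern holds in a conditional form. Certain from the text: cells are filled by an adherence count, only JOURNAL and FRAME patients can fail it, and 2.5.9 defines the same 84 in another way. Implied but not stated: an adherent-only analysis set.

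If non-adherers with complete WAI are left out, both primary comparisons are biased towards the interventions whenever adherence relates positively to WAI change, which the reasons the article gives for omissions make plausible. The size rests wholly on assumed inputs and runs from negligible (0.04 SD, 5.2%) to material (0.25 SD, 15.6%). If they are kept in, the bias largely disappears, and what remains is a larger intake over a longer window in the intervention cohorts.

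**What to change.** Amend 2.8.2 and align it with 2.5.9:

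1. Delete the adherence quota. Count towards each cell's 14 every enrolled patient with T1 and T2 WAI, whatever their adherence.
2. Make the primary analysis all such patients, by the cohort in which they enrolled.
3. State that patients who stop the intervention but not the study are still assessed at T2 and T3. Section 2.7.2 ends data collection only on withdrawal from the study, so this clarifies current practice. Say also that a non-adherer is not a drop-out, because 2.5.3 bars use of drop-outs' data for post-hoc analysis.
4. Report the numbers enrolled and lost in each cohort. A set defined by T2 WAI still selects on completion, and readers need to see whether losses differ between cohorts.
5. Give the adherent-only analysis as a sensitivity analysis, with one definition of adherence in place of the two present wordings.

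The cost is a short amendment, and fewer patients are needed rather than more. The estimate may be somewhat diluted by non-adherence. Recruitment began in summer 2025 (2.10), so the rule would change while it is running; non-adherers already enrolled with T1 and T2 WAI should be counted, and the date of the change reported.

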#### Plans to give access to the full protocol, participant level-data, and statistical code

2.8.3

The study protocol is published in this article, and final statistical analyses will be reported in the publications of study results. Due to privacy policies, patient data cannot be published, but aggregated data can be made available to researchers with a legitimate interest.

### Oversight and monitoring

2.9

#### Composition of the coordinating center and trials steering committee

2.9.1

The study is coordinated by the Department of Psychosomatic Medicine and Psychotherapy in Ulm. Statistical analyses are carried out at this department and at the Institute for Rehabilitation Medicine in Bad Buchau. The psychotherapeutic interventions will take place at the psychosomatic rehabilitation clinics Glotterbad and Schlossklinik Bad Buchau in Germany. At each study site, 42 participants will be included. The coordination team meets regularly once a week. Full staff meetings are held monthly.

#### Adverse event reporting and harms

2.9.2

All observed adverse events are recorded, reviewed by the study coordination team, and forwarded to the relevant ethics committees.

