### Objectives

2.1

The aim of the study is to investigate the effectiveness of two psychotherapeutic interventions that focus on positive expectations of patients with PCS during a psychosomatic rehabilitation program compared to treatment as usual alone (usual treatment in rehabilitation, no study intervention). Psychosomatic rehabilitation for patients with PCS in Germany follows a structured, multidisciplinary approach tailored to address both the persistent physical and psychological effects of the condition. Psychosomatic rehabilitation measures are paid for by the pension insurance provider, which checks compliance with the structured treatment. Rehabilitation begins with a thorough initial examination, which includes medical examinations, psychological screening, and functional assessments to identify the full range of symptoms, such as fatigue, shortness of breath, cognitive impairment, anxiety, and depression. Based on these assessments, structured treatment is individually tailored and comprises various therapeutic components designed to promote both physical and psychological recovery. The rehabilitation program typically combines physical therapy to restore endurance and muscle strength, especially in cases of post-viral fatigue and respiratory difficulties. Psychotherapy is frequently used to treat mental health issues such as anxiety, depression, and PTSD, which are common in patients with PCS. Relaxation techniques, such as progressive muscle relaxation or mindfulness meditation, are used to reduce stress and improve overall emotional regulation. Additionally, social and vocational counseling is integrated to support reintegration into working life and everyday routines and to help patients overcome challenges related to returning to work or dealing with social interactions. The rehabilitation program usually lasts between 3 to 4 weeks with intensive daily sessions, but may be extended depending on the patient’s individual progress and needs. Throughout the process, patients are closely monitored and the rehabilitation plan is adjusted as necessary. After completing treatment, patients often continue to receive care, for example through outpatient therapies or regular check-ups, to ensure lasting recovery and treat any remaining symptoms. The holistic approach aims to improve both physical functioning and mental health, ultimately enhancing the patient’s quality of life and ability to return their normal activities.

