### Participants

2.4

Patients with post-COVID syndrome (PCS) who are being treated at participating rehabilitation centers are included (ICD-10 codes U08.09 and U09.9; at least one persistent PCS symptom that persists for at least 12 weeks after the initial infection). Eligible patients are adults of working age, generally between 18 and 65 years old, as rehabilitation measures in Germany are financed by the pension insurance provider in order to maintain and restore patients’ ability to work. They must have sufficient knowledge of German to complete the questionnaires and understand the intervention and must be able to give written informed consent. Study participants receive comprehensive information about the study. Potential benefits and effects as well as possible side effects are explained. Additionally, participants are informed about data security and protection, and their rights as study participants. Study staff obtains written informed consent prior conducting baseline assessments. Patients with severe psychiatric conditions according to ICD-10 (e.g., psychotic symptoms, dementia/Alzheimer’s disease, known substance dependence and abuse [except nicotine]) or current suicidal ideation will be excluded. The following demographic variables are collected as part of the study: age, sex, immigration status, family/relationship status, children, place of residence (village, small town, medium-sized town, large city), level of education, occupational group, and employment.

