3	− Greeting with reflection on expectations: The patient should take up their expectations formulated in session I, read them through and reflect on them with the therapist. − Deepening, repetition, practicing of the imagination − Focus on side effect and coping expectations − Pleasant activities: Suggestions for pleasurable activities should be discussed with the patient using a provided list. The patient should select the examples that they consider suitable for themselves to build positive expectations for the future. − Summary and conclusion of the intervention	20–30 minutes

A therapeutic example from the PoCo-FRAME manual is described below. It is based on Laferton et al. (38, p. 24), has been translated into English, adapted to PCS, and supplemented.

Therapist: “I am very pleased that you have agreed to participate in our study. I believe you’ve made a good decision regarding the course of your rehabilitation. The goal of our collaboration is to explore your expectations regarding the success of your rehabilitation. Research has shown that patients who believe in the effectiveness of a treatment often experience better health outcomes afterwards. I´ll help you benefit as much as possible from this effect. I see my role as a confident companion on your journey. There may be times when you have questions or uncertainties — and we’ll address these together. It’s particularly important that we focus on your personal perspective. Please feel free to share your expectations in detail. Today, we’ll primarily focus on what you expect from the rehabilitation process. So, how about you start by telling me about your current situation and your expectations?”

The intervention is carried out as individual therapy in three sessions with one session per week (see **Table 1**). In addition, the patients in the FRAME-group receive a booklet summarizing the most important information from the individual sessions. The booklet also contains illustrations and worksheets that can be completed during or between sessions. Patients should bring the booklet to each session and read the information during the appointments. Therapists receive a documentation form for each patient, which must be completed. After each session, therapists must document which components of the intervention patients have completed.

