#### Provisions for post-trial care

2.5.6

It is assumed that participants will benefit from the intervention, resulting in an improvement in PCS symptoms. Adverse effects related to study participation are not anticipated.

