Objective measurements include computer and paper-based tests to assess cognitive performance, such as attention span, memory, and reaction times (Corsi Span Test and Color Stroop Test), 6-minute walk test, blood pressure, and 5-minute pulse measurement at rest to assess heart rate variability. Further measurements include clinical assessments of rehabilitation outcomes and medical evaluation of the ability to work (discharge letter) by the physician. The cognitive assessments are not part of routine clinical evaluations; they are specifically implemented for the purposes of this study.

A comprehensive range of outcomes was selected by a multidisciplinary research team to ensure the future provision of optimal support for patients.

The questionnaires are used in all three groups at the beginning baseline (T1; baseline), at the end of rehabilitation (T2), and six months after rehabilitation program (T3). Rehabilitation usually ends after 3 to 4 weeks. The final measurements for the study are taken during the last psychotherapy session in the final week.

Participants with PCS may experience difficulties using the screen and concentrating. To ensure their comfort and reduce any burden, we have made several adjustments available. Participants have the option to take breaks as needed, complete the questionnaires at their own pace, and even continue at a later time if necessary. Additionally, paper versions of the questionnaires can be provided upon request, and participants can also complete them in their rooms if this is necessary. The assessment sessions are expected to take between 70 and 90 minutes per assessment, depending on the individual condition and needs of the patient.

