#### Participant timeline

2.5.8

A schematic schedule for participants is depicted in **Table 2**.

**Table 2 T2:** Schedule for participants (T1, T2, T3 = time 1, time 2, time 3).

Assessments	T1 on admission to rehabilitation	T2 on discharge from rehabilitation	T3 6 months after rehabilitation
questionnaires	X (online in the clinic)	X (online in the clinic)	X (online from home)
cognitive tests	X (online in the clinic)	X (online in the clinic)	X (online from home)
blood pressure	X	X	
heart rate variability	X	X	
6-minute walk test	X	X	
discharge letter		X	

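### Adverse events are recorded only when observed, by staff who know the arm and see the arms for different lengths of time, with no common enquiry at T2 or T3

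*Protocol article*

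**What the plan says.** Section 2.9.2 of the protocol article is a single sentence: "All observed adverse events are recorded, reviewed by the study coordination team, and forwarded to the relevant ethics committees". It does not say who observes, whether patients are asked, or over what period.

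The surrounding sections set the opportunities to observe:

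- **Common to all arms.** All three groups receive the same regular rehabilitation, and the treating providers know each patient's condition (section 2.5.1). "The rehabilitation program usually lasts between 3 to 4 weeks with intensive daily sessions" (section 2.1), and the same section describes close monitoring. Questionnaires are completed at admission, "at the end of rehabilitation (T2), and six months after rehabilitation program (T3" (section 2.5.7).
- **JOURNAL.** Two short appointments with a research assistant. "Only a documentation form completed by the research assistant remains at the clinic" (section 2.5.2.1).
- **FRAME.** Three individual therapist sessions, timed in Table 1. "After each session, therapists must document which components of the intervention patients have completed" (section 2.5.2.2).
- **TAU.** No study session.

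Sections 2.5.4 and 2.8.2 describe the session forms as checklists of manual content delivered or left out, with reasons. They are not described as adverse-event forms. Table 2 (section 2.5.8) lists questionnaires, cognitive tests, physical measurements and the discharge letter, and the outcome list in section 2.5.7 names no harms item. Section 2.5.6 adds: "Adverse effects related to study participation are not anticipated".

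**The concern.** If an event counts only when someone happens to notice it, the number recorded depends on how often, and how attentively, each patient is seen. Here the additional contact depends on the arm, and the treating providers know the arm. After discharge the remaining planned contact is the online T3 assessment with its reminders, and none of that is described as an enquiry about adverse events.

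Two conclusions are at stake. An excess of events in FRAME could partly reflect closer observation. A low or zero count in any arm could reflect that nobody asked. The article's abstract hopes to equip more practitioners to support these patients, so readers will look for a statement on harms, and the method as written gives it little support.

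**Working it through.** The article states no figure on harms coverage, so there is none to reproduce.

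**1. Additional study contact per patient**

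- FRAME (Table 1): 50–60 + 20–30 + 20–30 = 90 to 120 minutes.
- JOURNAL (section 2.5.2.1): 2 × 20 = 40 minutes at most if the limit applies to each session. The wording could also mean 20 minutes in all.
- TAU: 0 minutes beyond the shared rehabilitation and assessments.

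**2. How large this is against the shared contact**

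The article does not give daily contact hours. Assume 2 to 5 hours per weekday for 3 to 4 weeks. Shared contact then runs from 2 × 5 × 3 × 60 = 1,800 minutes to 5 × 5 × 4 × 60 = 6,000 minutes.

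| Arm | Largest share of total contact | Smallest share of total contact |
|---|---|---|
| FRAME | 120/(1,800 + 120) = 6.25% | 90/(6,000 + 90) = 1.5% |
| JOURNAL (40 min) | 40/(1,800 + 40) = 2.2% | 40/(6,000 + 40) = 0.7% |

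So the difference between arms is real but small in minutes. What sets it apart is its kind: in FRAME it is one-to-one time with a therapist about the patient's state and expectations.

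**3. Share of the study period after discharge**

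Inputs: rehabilitation of r = 3 to 4 weeks (section 2.1) and T3 six months later (section 2.5.7), taken as about 26 weeks. Share = 26/(26 + r).

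- r = 3: 26/29 = 89.7%
- r = 3.5: 26/29.5 = 88.1%
- r = 4: 26/30 = 86.7%

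With six months counted as 24 weeks, the range is 24/28 = 85.7% to 24/27 = 88.9%. This is the share of time that falls after discharge with no listed adverse-event enquiry. It is not a measured share of missed events.

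**4. What a zero count would show**

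With 28 patients per arm and complete capture, 0 events gives a one-sided 95% upper bound of 1 − 0.05^(1/28) = 10.1%. That bound comes from the group size alone. If only a fraction c of events is noted, the bound on the true rate becomes 10.1%/c. Nothing in the article fixes c or makes it the same in each arm.

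**The case against.** The strongest reply is that the article condenses a fuller document, and that adverse-event definitions, windows and forms commonly sit there. This carries limited weight. Section 2.8.3 says that the study protocol is published in this article, and the point rests on the rule that is stated, not on missing detail.

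Other replies do stand, and they rule out stronger readings that a reader might infer:

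- **That recording stops at discharge, so that about 88% of follow-up is uncovered.** Section 2.9.2 gives no end date. The figure is a share of time only.
- **That TAU patients have no contact at which an event could be noted.** They share the daily rehabilitation, the in-clinic T2 assessment and the discharge letter, and section 2.5.5 has treatments documented in every arm.
- **That event counts are not comparable between arms.** The shared contact is much larger than the difference, and the article plans no between-arm comparison of events. Any ratio of capture rates between arms would be invented.
- **That worsening after discharge goes unseen.** T3 repeats the questionnaires, including depression, anxiety, somatic symptoms and work ability, in all arms.
- **That section 2.5.6 contradicts section 2.4.** Section 2.4 says of the consent information: "Potential benefits and effects as well as possible side effects are explained". Explaining possible effects is compatible with not expecting them.

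**Conclusion.** The point holds as a weakness of the stated method. Events are recorded passively, treating providers know the arm, additional contact differs (90 to 120 minutes, at most 40 minutes, and none), and no common adverse-event enquiry is listed at T2, at T3 or in the roughly 26 weeks between them. Equal ascertainment is not assured, and few or no recorded events would be weak evidence of safety.

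The size of any detection bias cannot be computed from the article, and the shared monitoring probably keeps it modest during the stay. The conclusion rests on reading the word for observed in section 2.9.2 as not requiring patients to be asked, and on treating providers being among those who observe, since no observer is named. The sample size, the error rates and the efficacy analysis are unaffected.

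**What to change.** 1. Add one identical adverse-event or worsening question to the existing T2 and T3 Unipark questionnaires in all three arms, and state this in section 2.9.2.
2. Pre-specify a deterioration measure from scores already collected (PHQ-9, GAD-7, PHQ-15 and WAI; T1 to T2 and T1 to T3). Tabulate it by arm for all participants whose data may be used. Section 2.5.3 bars post-hoc use of dropouts' data and section 2.7.2 ends collection at withdrawal, so the table cannot promise everyone who started. Give the number who withdrew in each arm beside it.
3. Report events known only from FRAME or JOURNAL session contacts separately, and do not compare them with TAU.

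Handing the review of events to the treating physicians would not help, because they know the arm as well.

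The cost is a short amendment, a minute or so of patient time, and more unspecific event reports in a population with varied symptoms. Recruitment began in summer 2025, so patients already past T2 or T3 will lack the new item. The score-based table still covers those of them whose data may be used.
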